#### Assessing the association between variables at baseline

The associations between variables will be assessed at baseline. For outcomes that have nominally significant differences between FRDA and control groups at baseline, we will assess their relationship with the number of GAA repeats on both alleles, age of onset and disease duration using Pearson or Spearman’s rank correlation. For instance, this analysis can be used to determine whether a monotonic relationship exists between a biomarker and disease severity. We will further assess the correlations between imaging and blood biomarkers with cognitive assessments for participants using a linear modelling framework.

#### Assessing the longitudinal changes over time

The within-person longitudinal slopes across the multiple visits will be estimated using a mixed linear model in which the slope for each participant is treated as a random effect. Within this framework we will assess the significance of a fixed effect that captures the difference in mean slope for individuals with FRDA with respect to controls. Due to the participant demographic in this study the analysis of within person slopes can give an indication of how age of onset and disease stage/severity can influence the subsequent clinical changes that occur within the parameters of participant demography.

#### Difference-in-difference analyses

Using baseline and 12-month follow-up data, we will determine whether the changeover 12-months differs between control and FRDA participants for each outcome. The difference between 12 months and baseline will be determined for each individual, and these differences will be compared between the two groups using a two-sample t-test or Mann-Whitney U-test.

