### Study design

The TRACK-FA study will involve the participation of children and adults with genetically confirmed FRDA and control participants. Participants will be allocated to one of four groups based on their age: ≥ 18 years, 11–17 years, 8–10 years, and 5–7 years. Control participants will be matched at the cohort level to the FRDA participants for age, sex, handedness, and years of education. A recruitment ratio of 1:1 (FRDA: control) will be used for those aged 5–10 years and a 2:1 ratio (FRDA: control) will be used for participants ≥ 11 years of age.

We aim to recruit a total of 200 individuals with FRDA and 104 control participants across seven testing sites. This number was informed by a power analysis (see below) and necessitated a multi-site collaborative network to achieve this goal. All participants will then be assessed at three visits [Visit 1 (V1), Visit 2 (V2), Visit 3 (V3)] with identical assessments; each visit will take place approximately 12 months apart and no more than two months before or after the 12-month interval.

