#### Analysis of cross-sectional differences at baseline

Individuals with FRDA and control groups will be compared at baseline using adjusted and unadjusted analyses. For unadjusted analyses, the two groups will be compared using the two-sample Student’s t-test or using the Mann-Whitney U-test for those variables that exhibit substantial skewness or otherwise do not match the assumptions of the two-sample t-test. For adjusted analysis a linear modelling approach will be used to predict case/control status, with demographic variables and site effects as covariates. This analysis will be conducted across all age groups represented in the study design, further enabling the possibility to observe differences in biomarkers between children and adults with FRDA and matched control participants. The baseline analysis provides the starting point from which functions such as rate of change can be derived for each of the parameters.

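### The 12-month FRDA–control comparison of change is unadjusted: it leaves out age, site and actual visit interval, and cannot carry the site term the plan itself requires

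*Protocol article*

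**What the plan says.** All places are in the protocol article.

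- **Difference-in-difference analyses.** For each outcome, the quantity analysed is a participant's 12-month value minus the baseline value. The test is then fixed: "these differences will be compared between the two groups using a two-sample t-test or Mann-Whitney U-test". No covariate, site term or actual interval enters, and the variance form of the t-test is not given.
- **Analysis of cross-sectional differences at baseline.** Adjusted and unadjusted analyses are both planned here. For the unadjusted one, "the two groups will be compared using the two-sample Student’s t-test or using the Mann-Whitney U-test for those variables that exhibit substantial skewness". This is the only place where Student's form is named.
- **Adjustment for potential site differences.** If baseline modelling detects site differences for an outcome, site is to enter as a random effect in a mixed model for the analyses of that outcome.
- **Study design.** Visits are about 12 months apart, "no more than two months before or after the 12-month interval". "We aim to recruit a total of 200 individuals with FRDA and 104 control participants across seven testing sites". The FRDA:control ratio is 1:1 at 5–10 years, and "a 2:1 ratio (FRDA: control) will be used for participants ≥ 11 years of age". Controls are matched on age, sex, handedness and education, but only at cohort level.
- **Status and timeline.** The FRDA targets are 110 adults, 82 aged 11–17 and 8 aged 5–10.
- **Assessing the longitudinal changes over time.** A separate random-slope mixed model tests the FRDA–control difference in mean slope. Its covariates and time scale are not stated.

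**The concern.** The baseline comparison has an adjusted version and the 12-month comparison of change does not. Three things that can affect a 12-month change are recorded and left unused.

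- **Age.** Growing children and adults are pooled. The Introduction itself says that developmental change must be told apart from degenerative change.
- **Site.** Table 3 gives the Skyra scanner different diffusion settings, so measured change or its noise may differ by site. The site rule asks for a model term that neither a t-test nor a Mann-Whitney test can hold.
- **Interval.** A change over 10 months and one over 14 months are both treated as a 12-month change.

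A fourth point is conditional. With groups of about 2:1, a pooled-variance t-test gives the wrong standard error if the two groups' changes differ in spread. The article makes unequal spread plausible: it says that rates of change depend on stage, and it expects different rates in the early and later sub-cohorts. Mann-Whitney is no remedy, since unequal spread affects it too and, as planned, it yields no estimate of the size of change.

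Objective 1 is to find the biomarkers most sensitive to change, and an analysis is planned after the 12-month visit. A test that wastes precision could make a useful marker look weak at that point.

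**Working it through.** **The plan's own figure.** None is stated for this test. The only power figure, n = 70 for d = 0.3, concerns change over 24 months. It agrees with a one-sided, one-sample calculation, ((1.645 + 0.842)/0.3)² = 68.7 (71 with the t distribution), and says nothing about a two-group comparison.

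**Inputs**
- Group sizes: 200 × 0.8 = 160 FRDA and 104 × 0.8 = 83 controls. This applies the planned 20% attrition to both groups (assumption). That loss is over 24 months, so 12-month numbers should be larger. Simulated sizes at 200 v 104 are almost the same.
- Ratio r of FRDA to control SD of 12-month change: not in the documents; assumed 0.8 to 2, with the control SD set to 1.

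**Step 1: standard error if variances are pooled**
- True SE = √(r²/160 + 1/83)
- Pooled SE ≈ √{[(160r² + 83)/243] × (1/160 + 1/83)}
- At r = 1.5: true SE = √(0.01406 + 0.01205) = 0.1616; pooled SE = √(1.823 × 0.01830) = 0.1826; ratio 1.13.
- Approximate type I error = 2[1 − Φ(1.96 × 1.13)] = 2[1 − Φ(2.215)] = 0.027.

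Simulated sizes (400,000 draws per setting) at 160 v 83, nominal 0.05:

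| SD ratio r | Pooled SE / true SE | Pooled t | Welch t |
|---|---|---|---|
| 0.8 | 0.93 | 0.068 | 0.050 |
| 1.0 | 1.00 | 0.050 | 0.050 |
| 1.25 | 1.07 | 0.036 | 0.050 |
| 1.5 | 1.13 | 0.027 | 0.050 |
| 2.0 | 1.21 | 0.018 | 0.050 |

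**Step 2: power for a difference of 0.3 FRDA SD**
- At r = 1.5 the difference is 0.45, which is 0.45/0.1616 = 2.785 true standard errors.
- Welch: Φ(2.785 − 1.96) ≈ 0.79. Pooled: Φ(2.785 − 2.215) ≈ 0.71–0.72. Simulation gives 0.79 and 0.71.
- Simulated power at r = 1.25 is 0.67 pooled v 0.71 Welch; at r = 2 it is 0.76 v 0.87. With equal SDs both are 0.60.

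**Step 3: visit timing**
- If change is proportional to time and intervals are uniform on 10–14 months in both groups, the variance of the interval in years is (4/12)²/12 = 0.00926.
- With a mean change of d SDs, the SD of change grows by √(1 + 0.00926d²): 0.04% at d = 0.3 and 0.5% at d = 1.
- Only timing that differs by group would bias the contrast. At the extreme, individual changes scale by 14/12 = 1.17 or 10/12 = 0.83.

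**Step 4: age**
- Under 18 in the FRDA target: 82 + 8 = 90 of 200.
- Controls: (110 + 82)/2 + 8 = 104, so the share aged 5–10 is 8/104 = 7.7% against 8/200 = 4.0% in FRDA.
- If those children's change differed by a full SD, the group contrast would shift by 0.077 − 0.040 ≈ 0.04 SD. This touches only the anatomical outcomes among the MRI measures, since children of 10 and under have no diffusion, QSM or spectroscopy.
- The precision lost by leaving age-related variation in the error cannot be sized, because the documents give no variance of change by age.

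**Step 5: site**
- A fixed offset at a site is the same at both visits and cancels in a within-person difference. What remains is any site difference in measured change or its variability.
- Side by side, the site rule calls for a mixed model with site for analyses of affected outcomes, while the 12-month section names two tests with no model. The article does not say which governs.

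**The case against.** The strongest reply is that little of this is established.

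- **Pooled variance.** Welch's test is also a two-sample t-test, and an article may leave the variance form to the analysis plan. This stands. A reader might infer a pooled test from the mention of Student's t-test, but that wording belongs to the baseline comparison alone.
- **False positives.** A reader might infer that the 2:1 groups make the 12-month test produce too many. The documents do not support that: no SD of change is given, and if FRDA, the larger group, varies more, a pooled test is conservative. Inflation needs controls to be the more variable group.
- **Timing.** A reader might take the 0.83–1.17 range as bias in the group contrast. It describes single participants at the edges of a symmetric window common to both groups. The article mentions limiting COVID-19 exposure for people with FRDA, which could shift their visits, but nothing shows that it did.
- **Age and site as confounders.** Age is matched at cohort level, the 5–10-year imbalance is worth about 0.04 SD at most under a large assumed difference, and constant site offsets cancel. So confounding is a weak charge. Matching the groups does not, however, remove age-related variation from the error term.
- **The mixed model already covers it.** The random-slope analysis is separate, addresses all visits, and does not change what is fixed for the 12-month comparison.

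What the reply does not remove is that the article fixes a raw difference and an unadjusted test for every outcome, and that this does not fit its own site rule.

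**Conclusion.** The point holds as one of efficiency and internal consistency. As written, the 12-month comparison takes no account of age, site or actual interval and cannot carry the site term required elsewhere. That conflict is the firmest part and rests on the text alone.

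The size of the variance problem is conditional on pooling, on about 160 v 83 completers, and on an assumed SD ratio. For ratios of 1.25 to 2 the true type I error is about 3.6% to 1.8%, with roughly 0.05 to 0.11 of power lost for a difference of 0.3 FRDA SD. At a ratio of 0.8 the type I error is about 6.8%. Timing and the young-child imbalance are minor unless intervals differ by group. The comparison is worth correcting because the remedy is cheap and uses data already collected; nothing here shows that its results would be invalid.

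**What to change.** 1. For the 12-month contrast, regress each participant's change, annualised by the actual interval, on diagnosis, age, sex and site, with heteroscedasticity-robust (Welch-type) standard errors. Report the adjusted difference with its confidence interval.
2. Keep Mann-Whitney as a sensitivity check.
3. Reconcile the difference-in-difference section with the site rule: say whether the rule covers analyses of change and, if so, whether site terms in this regression satisfy it.
4. Name Welch's test for the unadjusted baseline comparison.

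The cost is analysis-plan wording, slightly more analysis work and a few degrees of freedom, about six of them for seven sites. Annualising scales measurement noise by 12/10 = 1.2 at 10 months and 12/14 = 0.86 at 14 months; the robust errors allow for this. A heavier model, with site-by-time terms and group-specific residual and random-slope variances, is not needed for this contrast: with only two visits those variances can barely be separated.

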#### Stratified analysis

Additional analyses on data stratified by variables such as disease duration, age of onset and GAA repeat length will be conducted. This stratified analysis will determine whether sensitivity of a biomarker differs across subgroups of FRDA, e.g.: a specific measure has greater sensitivity to change in individuals with an early onset of disease compared with those who have later onset of disease.

#### Interim analyses and accounting for missing data

Interim analysis will be performed after the completion of each visit (baseline, 12-month and 24-month time points). There are likely to be instances of missing data in this study, due to the study requiring interstate travel to attend testing, participant health concerns and normal participant dropout. We had increased our target sample size by 25% to account for 20% anticipated participant attrition, and if required the consortium will consider the recruitment of additional participants in order to ensure that the analysis has the necessary statistical power. Participants with missing data for just one of the three visits will be included under a missing at random assumption for longitudinal mixed linear modelling.

*Data confidentiality and storage*. Participants’ personal information, genetic information, clinical, cognitive, mood and biospecimen data generated in this study will be de-identified by assigning a unique study identification number. All raw, pre-processed (defaced) and processed MRI images will be stored in the Monash XNAT platform [78]. Defacing of 3D T1 and T2 MRI data will be conducted using MaskFace [79] version 10.15.18 [80]. To ensure consistency, the team at the University of Minnesota provided each site with a Docker or Singularity container containing scripts to automatically sort the data and deface the brain T1 and T2 images before upload to XNAT [78]. The REDCap database (Helix, Monash University) [81] will be used to store all other study data. All paper-based case report forms (CRFs) will be kept in a locked cabinet to be accessed by authorised personnel at each site according to the Good Clinical Practice guidelines. Data entry into REDCap will follow standard double data entry processes, with responsibility for accuracy lying with individual sites. The central study coordinator will provide overall oversight of data management through randomised checks of a proportion of REDCap entries.

Academic sites and industry collaborators will have secure access to both raw and processed data within the Monash XNAT and REDCap platforms throughout the duration of the study in accordance with the study agreements. Data may also be made available to third parties at the completion of the study, and upon request, provided that they obtain approval from the TRACK-FA Steering Committee. All records and samples will be stored according to local IRB requirements at each site.

*Quality management*, *assurance*, *and control*. Rigorous pilot testing of n = 5 control participants, at each study site, was undertaken prior to study commencement. All pilot images were examined by the Minnesota University imaging team prior to commencement of the study to verify the-quality of MRI data.

IXICO has been appointed as a contract research organisation (CRO) through a fee for service contract. IXICO will perform independent quality control and data analysis of brain anatomical imaging and brain diffusion imaging data for one third of TRACK-FA subjects. 300 datasets will be sampled by a TRACK-FA biostatistician who will not be provided the unique study IDs of the selected datasets. Specific analyses performed by IXICO will include volumetric MRI of the cerebellum and brain stem and DTI for cerebellar peduncles, using IXICO‘s own software and pipelines, which are different from pipelines used by academic sites for primary outcome measures. IXICO will conduct interim analyses at 50% of total enrolment and 100% of total enrolment at each time point. Quality control of MRI procedures will be upheld by conducting phantom quality assurance testing. This testing will be conducted by each study site monthly and will be uploaded to XNAT upon which time any discrepancies will be notified, and modifications will be made to the process at that specific site.

Furthermore, rigorous training has been provided across all study sites to avoid any potential bias in clinical, cognitive and mood test administration. Videos have also been recorded for training purposes and monthly coordinator meetings ensure that study sites have an opportunity to trouble shoot any issues at the local level.

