#### Stratification of participants

The Friedreich’s Ataxia Rating Scale (FARS) functional staging for ataxia scale [51], will be used to stratify participants with FRDA into disease stage subgroups as outlined in Table 2. At the time of enrolment, we aim to have 55% of participants in FARS functional stages 0–2, 35% in the functional stages 3–4 and 10% in functional stage 5. Individuals in stage 6 will not be enrolled. This will create a cohort largely representative of those earlier in the disease process. Those earlier in the course of disease, particularly those who are still ambulant, progress at a much faster rate [27, 52, 53], hence detecting progression through proposed biomarkers in this cohort may be more efficient.

**Table 2 pone.0269649.t002:** The FARS Functional Staging for Ataxia scale describing the clinical presentation at each stage.

Friedreich’s Ataxia Rating Scale Functional Staging for Ataxia Scale	
Functional staging	Clinical presentation
Stage 0	Normal
Stage 1	Minimal signs detected by physician during screening. Can run or jump without loss of balance. No disability
Stage 2	Symptoms present, recognized by patient, but still mild. Cannot run or jump without losing balance. The patient is physically capable of leading an independent life, but daily activities may be somewhat restricted. Minimal disability
Stage 3	Symptoms are overt and significant. Requires regular or periodic holding onto wall/furniture or use of a cane for stability and walking. Mild disability. (Note: many patients postpone obtaining a cane by avoiding open spaces and walking with the aid of walls/ people etc. These patients are graded as stage 3.0)
Stage 4	Walking requires a walker, Canadian crutches or two canes and or other aids such as walking dogs. Can perform several activities of daily living. Moderate disability
Stage 5	Confined but can navigate a wheelchair. Can perform some activities of daily living that do not require standing or walking. Severe disability
Stage 6	Confined to wheelchair or bed with total dependency for all activities of daily living. Total disability

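### The stated rule for the longitudinal mixed model implies that participants seen only once are left out, which weakens the missing-at-random protection it claims and can bias the mean slope

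*Protocol article*

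**What the plan says.** Under Study design, the protocol article plans three visits about 12 months apart: "All participants will then be assessed at three visits". Under Assessing the longitudinal changes over time, within-person slopes are "estimated using a mixed linear model in which the slope for each participant is treated as a random effect", and the quantity tested is "the significance of a fixed effect that captures the difference in mean slope for individuals with FRDA with respect to controls".

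The rule for incomplete data in that mixed model is under Interim analyses and accounting for missing data: "Participants with missing data for just one of the three visits will be included under a missing at random assumption". Nothing is said about participants who miss two visits. The same section expects data to be missing "due to the study requiring interstate travel to attend testing, participant health concerns and normal participant dropout", and says of attrition: "We had increased our target sample size by 25% to account for 20% anticipated participant attrition". It does not say how that 20% divides between one and two missed visits.

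Under Stratification of participants, the article states that progression depends on stage: "Those earlier in the course of disease, particularly those who are still ambulant, progress at a much faster rate".

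**The concern.** The sentence sets a limit (one missed visit) and a justification (missing at random), and the two do not fit together. Under missing at random, a likelihood analysis may ignore the missingness mechanism because the data that predict missingness are in the model. For someone lost after visit 1, those data are the baseline record. If it is removed, the analysed sample is selected on baseline, and the model cannot correct for the selection.

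The mean slope can then move in two ways:

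- **Slope related to baseline level.** If people with worse baselines progress more slowly or faster, losing them changes the average slope of those who remain.
- **Regression to the mean.** Even when true slope and true level are uncorrelated, a poor baseline reading is partly measurement error. If poor readings predict loss, those who stay have baselines that are too good on average, and their later visits drift back. This looks like extra progression.

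Objective 1 is to find the biomarkers most sensitive to change, and the Discussion expects the data to inform the design of future trials. A slope error that differs between biomarkers would affect both uses.

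**Working it through.** **The plan's own attrition figures.** The article doubles 70 to 140 and adds 25% for 20% attrition. This is consistent: 140 / 0.80 = 175 and 140 × 1.25 = 175; 200 was selected. Attrition of 20% of 200 is 40 FRDA participants. The number seen only at baseline is not given. Shares of 5% and 10% would be 10 and 20 people; a 20% share would mean that all planned attrition falls before visit 2. The basis of n = 70 plays no part in this point.

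**Inputs from the article.** Visits at 0, 1 and 2 years; a linear mixed model with random slope; an effect size of 0.3 for the change over 24 months.

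**Assumed inputs, none of them in the document.** Random-intercept SD 1; slope SD 0.15 per year; residual variance 0.05 or 0.15; intercept-slope correlation; share seen only at baseline; log-odds of loss after visit 1 per SD of worse baseline.

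**True slope.** The variance of the 24-month change is 4 × 0.15² + 2 × residual variance, and the yearly slope is 0.3 × SD / 2.

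- Residual variance 0.05: SD = √(0.09 + 0.10) = 0.436; slope = 0.0654.
- Residual variance 0.15: SD = √(0.09 + 0.30) = 0.624; slope = 0.0937.

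**Simulation.** Each scenario used 400,000 participants, so that sampling noise is small. Loss after visit 1 was logistic in the observed baseline, which is missing at random. The model was fitted by maximum likelihood twice, with and without the baseline-only participants.

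*Loss unrelated to baseline (log-odds 0).* Excluding them left the slope within about 1.2% of the truth, which is noise.

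*Loss dependent on the outcome's own baseline (log-odds 1 per SD), baseline-only participants excluded.* Error in the mean slope, residual variance 0.05 / 0.15:

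| Intercept-slope correlation | 5% baseline-only | 10% | 20% |
|---|---|---|---|
| -0.3 | +5.7% / +5.8% | +9.5% / +11.4% | +17.8% / +20.2% |
| 0 | +2.1% / +3.2% | +3.9% / +8.0% | +6.0% / +14.0% |
| +0.3 | -1.3% / +1.4% | -1.9% / +2.9% | -5.1% / +4.8% |

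The middle row is regression to the mean alone. Extending the correlation to -0.5 raises the upper end for 5-10% baseline-only to about +14%.

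*Loss dependent on a severity score correlated 0.4 with the imaging baseline.* With 5-10% baseline-only, log-odds 1 and correlations from -0.5 to +0.3, the error is about -2% to +5%.

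*All participants kept.* The slope is within about 1.5% of the truth throughout.

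These figures concern the FRDA slope. The bias in the tested quantity is the FRDA bias minus the control bias, and it was not computed, because the document gives nothing on loss among controls.

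**The case against.** The strongest reply is that the sentence excludes nobody. It can be read as reassurance that incomplete cases are kept, and an article may leave the handling of people seen once to the full analysis plan. It is true that no exclusion is stated, so a reader who infers that the plan drops these participants goes beyond the text. But the sentence is an inclusion rule with a limit, tied to a named model and a named assumption. An analyst who followed it would leave one-visit participants out. It is a rule worded badly, not a detail left for later.

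A reader might also infer that the slope is certain to be biased. The documents do not support that. They name travel, health concerns and ordinary dropout, and the section on COVID-19 adds lockdowns and reluctance to travel. They do not say that any of these follows disease severity or the baseline imaging value. Nor does the statement on faster early progression settle the direction, since it rests on clinical course. For imaging, the Introduction says that dentate iron change accelerates with progression while dentate atrophy is fastest early and then plateaus.

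Larger figures are also tempting. With 12% lost after visit 1 and log-odds of 1-2 per SD, the overstatement reaches 11-25% at correlations of -0.3 to -0.5. Those inputs are at the strong end, and the 12% alone would be more than half of the planned attrition.

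Two further points stand. Loss common to both groups would partly cancel in the slope difference. And the error is modest beside sampling error: with 160 of 200 retained and d = 0.3, the relative standard error of the mean change is about (1/√160)/0.3 = 26%, so +14% is roughly half a standard error and +5% about a fifth. Sampling error shrinks when data are pooled with later studies, however, and this bias does not.

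**Conclusion.** The point holds as a wording defect with a possible, not a certain, effect. On its natural reading the rule limits the mixed model to participants with at least two visits, and that undercuts the missing-at-random claim in the same sentence. The FRDA mean slope can be biased if loss after visit 1 depends on baseline, and the FRDA-control difference can be biased if that loss differs between the groups. If the loss is unrelated to baseline there is no bias, and if few people are seen only once there is little.

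The sizes above rest on assumed shares, log-odds, correlations and variances. The mechanism does not depend on those particular values, but the size and sign do. No bias in the group difference has been shown.

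**What to change.** Replace the sentence with: *All participants with at least one evaluable visit are included in the mixed model, fitted by (restricted) maximum likelihood, under a missing at random assumption.*

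The cost is one sentence. The baseline records will already have been collected, and the model in the plan accepts them without change. No further covariate is needed. In particular, adding baseline FARS stage is not part of this fix: stage is assessed only in participants with FRDA, a main effect of stage adjusts level and not slope, and a stage-by-time term would change what the mean slope means.
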